## 6.2 Experimental Arm (Arm 2)

The GTVs and PTVs used for planning in Arm 2 are those that have been defined in Arm 1 for that particular patient. Patients randomized to Arm 2 will undergo IMRT planning. Treatment can be delivered using static beams (either 3D-conformal radiotherapy, or intensity-modulated) or rotational therapy (volumetric modulated arc therapy, or tomotherapy). Priority will be placed on generating clinically acceptable plans while minimizing complexity, planning time and treatment time.

ES-PTV will be optimized and the esophagus will take priority over PTV in the optimization process. In most cases, ES-PTV will need to be compromised in order to achieve esophageal constraints.

For plans in Arm 2, dose constraints are as follows:

- The maximum dose within the body is limited to no more than 2 cm^3 receiving 115% or more of the prescription dose.
- The allowable dose to “lung\_eval” is based on the values from the fields placed for that particular patient. The V16 value (for 30 Gy in 10 fractions) or the V13 value (for 20 Gy in 5 fractions) may not exceed the value recorded from the APPA fields by more than 3%. For example:
  - if a patient has a V16 value of 30% with the APPA fields (prescription dose 30 Gy in 10 fractions), the V16 value with the IMRT plan may not exceed 33%.
  - if a patient has a V13 value of 30% with APPA fields (prescription dose 20 Gy in 5 fractions), the V13 value with the IMRT plan may not exceed 33%
  - For all patients, the V5 should be less than 60%.
- The dose to the esophagus should be as low as achievable. Underdosage of the PTV is allowed and will often be required. The following approach should be used:
  - **Step 1: A plan is designed constraining the maximum dose to the esophagus to 80% of the prescription dose** (i.e. 24 Gy if using 30 Gy in 10 arm and 16 Gy if using 20 Gy in 5 fractions). This constraint is met regardless of GTV and PTV coverage within the Esophagus\_ring. In some cases, if there is GTV within the Esophagus\_ring, small areas of that GTV may receive as little as 80% of the prescription dose.
    - 95% of the ES-PTV outside of the Esophagus\_ring should still

receive at least the same D95 as in Arm 1. Better PTV coverage is allowed as long as lung constraints are met.

- **Notes:** suggested optimization parameters will be provided. The maximum esophageal dose is defined as the dose to the hottest 0.1 cc.
- **Step 2. Once this is achieved, the dose to the esophagus should be further reduced if possible**, while ensuring that all GTV within the Esophagus\_ring receives at least 80% of the prescription dose, and 95% of all ES-PTV outside the Esophagus\_ring receives at least 95% of the prescription dose.

#### 6.2.1 Example Plans for Arm 2

The plans on the following page demonstrate the esophageal sparing technique for two cases prescribed 30 Gy in 10 fractions, one where the GTV is in close proximity to the esophagus (left) and one not in close proximity (right). Structures are: GTV (blue), PTV (red), esophagus (green). The same color scheme applies for the DVHs, with the “lung evaluation” structure in light blue, the dotted lines representing the IMRT plan, and the solid line representing the APPA plan.

Notes:

- i. The fields in Arm 1 should represent the fields that would be used in standard clinical practice, and dosimetric coverage of GTV and PTV is not protocol-specified.
- ii. In the plan at left, esophageal sparing stops once <0.1 cc of esophagus is receiving ≤80% of the prescription dose. This ensures that the GTV adjacent to the

esophagus receives at least 80% of the prescription dose. In the plan at right, more esophageal sparing can be achieved.

- iii. For this prescription, V16 is the parameter of interest for the lung evaluation structure. The V16 in the IMRT plan cannot be >3% more than in the APPA plan, and the V5 must remain below 60%
- iv. In some cases, PTV coverage is better with IMRT than with the standard clinical fields. This is allowed, but not required.
- v. In a situation where the esophagus is abutting the GTV, GTV underdosage (<80% of the prescription dose) is permissible, provided that this volume is <1cc.

[figure not shown]

**Figure 2: Esophageal Sparing for two cases prescribed 30 Gy in 10 fractions, one where the GTV is in close proximity to the esophagus (left) and one not in close proximity (right). Legend: GTV (blue), PTV (red), esophagus (green). The same color scheme applies for the DVHs, with the “lung evaluation” structure in light blue, the dotted lines representing the IMRT plan, and the solid line representing the APPA plan.**

### 6.3 Image guidance

Daily image guidance is required in both arms, and may be in the form of MV, kV or CBCT imaging. In arm 2, daily CBCT is preferred.

### 6.4 Central Collection of Imaging Data

Imaging data will be centrally collected through the Quantitative Imaging for Personalized Cancer Medicine (QIPCM) platform ([qipcm.technainstitute.com](http://qipcm.technainstitute.com)), which provides centralized storage and data analysis tools for medical imaging, and is compliant with national and international privacy regulations. Scans collected by QIPCM will include the planning scan, POP and ES-IMRT radiation dose distributions, and baseline/follow-up CTs of the thorax. Note the follow-up CTs are optional, but those performed will be collected through QIPCM. Participating sites will be provided separate instructions regarding the uploading procedure.

### 6.5 Registration procedure and Data Collection:

#### Registration/Randomization Procedure

1. Call the coordinating centre at the Cancer Clinical Research Unit [contact] [name]) of London Health Sciences Centre (LHSC) to notify of new randomization and ask for the next patient ID number.
2. Complete the Enrollment form in REDCap prior to randomization. Signed letter of information to be completed and uploaded on to the REDCap database.

3. Notify the coordinating centre that you have completed the enrollment form and uploaded the required documents.
4. If the patient is eligible the coordinating centre will confirm via email and provide the randomization arm.

#### Data Collection

- For radiation plans that require feedback (e.g. test plans before activation), centres must notify the coordinating centre by phone or email once test plans are uploaded to QIPCM. The coordinating centre will then notify the PIs that the plans are ready to review. After review, the PI will report the acceptability of the plans to the coordinating centre, who will then inform the submitting site.
- All SAEs will be reported using a paper form faxed to the coordinating centre, followed by a call to the coordinating centre immediately after faxing.
- All other data will be collected using REDCap, a web based electronic database.

## **7.0 ADVERSE EVENTS**

### **7.1 Definitions**

*Adverse Event (AE)* or reaction is any unfavorable and unintended sign (including an abnormal laboratory finding), symptom, or disease temporally associated with the use of a medical treatment or procedure that may or may not be considered related to the medical treatment or procedure.

*Serious Adverse Event (SAE)* or reaction as defined in the ICH Guideline: Clinical

Safety Data Management: Definitions and Standards for Expedited Reporting, E2A

Section IIB includes any untoward medical occurrence that at any dose:

- Results in death
- Is life-threatening (refers to an event in which the patient was at risk of death at the time of the event; it does not refer to an event which hypothetically might have caused death if it were more severe.)
- Results in persistent or significant disability/incapacity
- Requires in-patient hospitalization or prolongation of existing hospitalization
- Is a congenital anomaly/birth defect

Important medical events that may not be immediately life-threatening or result in death or hospitalization may be considered a serious adverse event, when, based upon medical and scientific judgment, they may jeopardize the patient or may require intervention to prevent one of the other outcomes listed in the definition above.

*Unexpected adverse* reaction is one that the nature and severity is not consistent with the applicable product information (e.g., Investigator's Brochure or Product Monograph, described in the REB/IRB approved research protocol or informed consent document), or occurs with more than expected frequency.

## 7.2 Causality (attribution)

An adverse event or reaction is considered related to the research intervention if there is a reasonable possibility that the reaction or event may have been caused by the research intervention (i.e. a causal relationship between the reaction and the research intervention cannot be ruled out by the investigator(s)).

The relationship of an AE to the study treatment (causality) will be described using the following definitions:

### **Unrelated**

- Any adverse event for which there is evidence that an alternative etiology exists or for which no timely relationship exists to the administration of the study treatment and the adverse event does not follow any previously documented pattern. The adverse event, after careful consideration by the investigator, is clearly and incontrovertibly due to causes other than the intervention.

### **Unlikely**

- Any adverse event for which the time relationship between the study treatment and the event suggests that a causal relationship is unlikely and/or the event is more likely due to the subject's clinical condition or other therapies concomitantly administered to the subject.

**Possible**

- Any adverse event occurring in a timely manner after the administration of the study treatment that follows a known pattern to the intervention and for which no other explanation is known. The adverse event, after careful consideration by the investigator, is considered to be unlikely related but cannot be ruled out with certainty.

**Probable**

- Any adverse event occurring in a timely manner after the administration of the study treatment that follows a known pattern to the intervention and for which no other explanation is known. The adverse event, after careful consideration by the investigator, is believed with a high degree of certainty to be related to the intervention.

**Definitely Related**

- Any adverse event occurring within a timely manner after administration of the study treatment that is a known sequela of the intervention and follows a previously documented pattern but for which no other explanation is known. The adverse event is believed by the investigator to be incontrovertibly related to the intervention.

### 7.3 Severity

The severity of adverse events will be evaluated using the Common Terminology

Criteria for Adverse Events (CTCAE) v4.0 grading scale (see (<http://ctep.cancer.gov>)).

Grade 1: Mild

Grade 2: Moderate

Grade 3: Severe

Grade 4: Life-threatening or disabling

Grade 5: Death

Note: The term “severe” is a measure of intensity: thus a severe adverse event is not necessarily serious. For example, nausea of several hours’ duration may be rated as severe, but may not be clinically serious.

### 7.4 Immediately Reportable Adverse Events

Any grade 4 or 5 adverse reaction that is definitely, probably, or possibly the result of protocol treatment must be verbally reported to the Principal Investigator and the coordinating centre within 24 hours of discovery, and to the approving research ethics board (REB) as per their reporting guidelines.

Local and non-local SAEs will be reported to the applicable REB as per their reporting guidelines. All serious, unexpected adverse events or reactions regardless of causality

will be reported within 7 days of discovery to the pertinent REB.

NOTE: conditions that are NOT related to protocol treatment are not considered a SAE in this protocol: e.g. hospitalizations for routine procedures, disease progression, toxicity from chemotherapy delivered >2 weeks after radiotherapy.

The Principal Investigator should also comply with the applicable regulatory requirement(s) related to the reporting of unexpected serious adverse drug reactions to the regulatory authority(ies).

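### The note in section 7.4 makes relatedness a condition of being an SAE, contradicting the SAE definition in 7.1 and, for unexpected events judged unrelated, the causality-free reporting rule in 7.4

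*Protocol*

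**What the plan says.** **Definitions (Protocol 7.1).** An adverse event is one "that may or may not be considered related to the medical treatment or procedure". An SAE "includes any untoward medical occurrence that at any dose" leads to one of the listed outcomes, such as death, a threat to life, or hospital admission. Neither definition depends on cause. An event also counts as unexpected if it happens more often than anticipated.

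**Reporting (Protocol 7.4).** SAEs go to the research ethics board (REB) under that board's own guidelines. In addition, "All serious, unexpected adverse events or reactions regardless of causality" must reach the REB within 7 days.

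**The note (end of Protocol 7.4).** It states that "conditions that are NOT related to protocol treatment are not considered a SAE in this protocol". Its examples are "hospitalizations for routine procedures, disease progression, toxicity from chemotherapy delivered >2 weeks after radiotherapy".

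**Treatment in Arm 2 (Protocol 6.2).** For the PTV, "Underdosage of the PTV is allowed and will often be required". Where gross tumour lies inside the esophageal ring, "small areas of that GTV may receive as little as 80% of the prescription dose". Note v of 6.2.1 allows less than 1 cc of abutting GTV to fall below 80%.

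**Who attributes, and with what knowledge.** Section 7.2 leaves causality to the investigator. Under section 6.5 the coordinating centre tells the site the allocated arm. The only blinding described is that of the Data Safety Monitoring Committee (DSMC) at the interim analysis (10.6).

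**The concern.** The note turns an outcome-based definition into one that depends on a causal judgement. A site that follows 7.1 and a site that follows the note will handle the same event differently.

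Disease progression is a sensitive example in this trial. The experimental technique trades some target dose for esophageal sparing, so progression near the esophagus could be a consequence of protocol treatment. The note classes it in advance as unrelated, and the people applying the note know the arm.

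What is at stake is a specific gap in the safety record: serious, non-fatal events that a site labels as progression, for example an admission for worsening thoracic disease. Section 2.1 lists no endpoint for progression or local control, and section 9.0 makes follow-up chest CT optional. No other planned measure is therefore dedicated to such events.

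**Working it through.** No arithmetic bears on this point. The check is to apply each rule to the same kinds of serious event.

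| Serious event | SAE under 7.1? | 7-day REB rule in 7.4 applies? | SAE under the note? | Result |
|---|---|---|---|---|
| Related to treatment | Yes | Only if unexpected | Yes | No conflict |
| Unexpected, judged unrelated | Yes | Yes | No | Note conflicts with 7.1 and with the 7-day rule |
| Expected disease progression | Yes | No | No | Note conflicts with 7.1 only |

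1. **Second row.** The event is not an SAE under the note, so it need not go on the faxed SAE form that section 6.5 prescribes. It is still owed to the REB within 7 days. The coordinating centre's SAE file and the REB's file can then differ.

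2. **Third row.** Progression is ordinarily expected in stage IV disease, or in stage III not eligible for curative treatment (4.1), so the 7-day rule is usually not engaged. The conflict is between the definition in 7.1 and the exemption in the note. If progression occurred more often than anticipated, 7.1 would make it unexpected and the event would move to the second row.

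3. **Attribution.** Section 7.2 treats an event as related when causality cannot be excluded, and reserves its unrelated category for events beyond doubt due to something else. Naming progression in the note invites sites to skip that case-by-case test.

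4. **Where the same event could still appear.**
   - Death: in overall survival, which counts all causes (2.1, 9.1.1) and is shown by arm to the DSMC at the 30-patient interim (10.6).
   - Toxicity: CTCAE scores are recorded at each visit (9.0, Appendix 2), and the DSMC examines any reported grade 3-5 toxicity (10.6).
   - Quality of life: the lung subscale and EQ-5D are completed at each visit (9.0).
   - Non-fatal progression: no dedicated endpoint. The protocol does not say whether such an event would be scored as a toxicity.

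The contradiction thus affects SAE reporting. The events most exposed are serious, non-fatal and labelled progression.

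**The case against.** The strongest reply is that this is a wording inconsistency with little effect on what the trial learns. DSMC review under 10.6 is triggered by toxicity grade, not by SAE status. The between-arm safety test in 10.5 uses toxicity of grade 2 or higher, again without reference to SAE status. Deaths cannot be filtered out of overall survival. Exempting expected progression from rapid reporting in advanced lung cancer is a defensible choice. Much of this stands, and it limits the point.

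Four stronger readings are tempting, and the protocol does not support them.

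- **A reader might infer that the DSMC sees only a list already screened by sites.** The note changes the SAE label. It does not remove events from the CTCAE record, and adverse events are defined irrespective of relatedness.
- **A reader might infer that progression is a harm peculiar to Arm 2.** It occurs in both arms. Target coverage in Arm 1 is not specified, coverage is sometimes better with IMRT (6.2.1, notes i and iv), and Step 1 in 6.2 ties ES-PTV coverage outside the ring to the Arm 1 D95.
- **A reader might infer that a few misfiled events would decide the DSMC threshold of more than 5% grade 4/5 toxicity.** With 30 patients, 0.05 × 30 = 1.5, so 2 events exceed it. With 90, 0.05 × 90 = 4.5, so 5 do. But the threshold is set on toxicity rates, so missing SAE labels do not by themselves change it.
- **A reader might put a number on the lost events by assuming a rate.** The protocol gives no rate of serious progression events.

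What the reply does not remove is the contradiction itself, or the absence of a dedicated route for non-fatal events called progression. Overall survival misses them, and visit toxicity scoring is not designed to capture them.

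**Conclusion.** The point holds in a limited form. The note in 7.4 contradicts the SAE definition in 7.1 for every serious event judged unrelated. It contradicts the 7-day REB rule only for those that are also unexpected. Serious non-fatal events labelled progression may be missing from SAE reporting, in a trial whose experimental arm plans some target underdosage.

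The size cannot be derived from the protocol. No effect on the primary endpoint, its analysis or the sample size is shown, and nothing shows that sites would attribute events differently by arm. The conclusion that attribution is made with knowledge of the arm rests on section 6.5 and on the absence of any described site blinding; the protocol does not call the trial open-label.

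A statistical analysis plan could not repair this, because events never recorded as SAEs cannot be tabulated as SAEs later. The change is worth making in the protocol.

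**What to change.** Reconcile 7.1 and 7.4 as follows.

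- Record every event that meets the 7.1 criteria as an SAE, whatever its attribution.
- Hold attribution in a separate field, using the categories in 7.2.
- Reword the note so that any exemption, such as for disease progression or routine admissions, is from expedited reporting and not from the SAE definition. Expedited reporting can still depend on relatedness and expectedness.
- Tabulate SAEs by arm for the DSMC, overall and by attribution.

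The cost is a wording change and more SAE forms at the sites. No new visits, tests or procedures are needed.

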#### **8.0 SUBJECT DISCONTUATION/WITHDRAWAL**

Subjects may voluntarily discontinue participation in the study at any time. If a subject is removed from the study, the clinical and laboratory evaluations that would have been performed at the end of the study should be obtained. If a subject is removed because of an adverse event, they should remain under medical observation as long as deemed appropriate by the treating physician.

#### **9.0 FOLLOW-UP EVALUATION AND ASSESSMENT OF EFFICACY**

Patients will be seen at 2 weeks post radiotherapy. This assessment will be prior to the potential start of any systemic treatment. Further follow-up will be at 2 weeks, 4 weeks, 8 weeks, 3, 6 and 12 months post-radiotherapy. At each visit, the oncologist will conduct a history and physical examination, and CTC-AE toxicities recorded. The FACT-G, its ECS

and LCS subscales, as well as the EQ-5D quality of life questionnaire are to be completed at each visit. (Appendix 2). Please note that if either the treating physician or patient prefer, visits at 4 and 8 weeks may be substituted with a telephone interview (by the research coordinator or physician) to complete quality of life questionnaires and toxicity data. CT chest, is suggested but optional at 3, 6, 9 and 12 months, with additional surveillance imaging and/or laboratory investigations at the discretion of the treating oncologists. Further treatment, (e.g. chemotherapy, targeted therapy, immunotherapy) is at the discretion of the treating oncologists.

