### **2.1 Endpoints**

#### **Primary Endpoint:**

1. Esophageal quality of life
  - Measured by the Esophageal Cancer Subscale (ECS) of the FACT-E

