#### ***Primary Endpoint***

Esophageal quality of life will be calculated by tabulating FACT-E scores at 2 weeks, with differences between groups tested using the Student's t-test.

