## Appendix 2 – Follow-up schedule

|                       | pre-RT                       | 2 weeks post RT | *4, 8 weeks post RT            | Months 3, 6, 12        |
|-----------------------|------------------------------|-----------------|--------------------------------|------------------------|
| History and physical, | X                            | X               | Only if clinic visit is booked | X                      |
| *Toxicity scoring     | X                            | X               | X                              | X                      |
| CT chest              | X                            |                 |                                | Suggested and optional |
| Bone scan             | Recommended if bony symptoms |                 |                                |                        |
| CT or MRI brain       | Recommended if CNS symptoms  |                 |                                |                        |
| *FACT-E and FACT-L    | X                            | X               | X                              | X                      |
| *EQ-5D                | X                            | X               | X                              | X                      |

\* QoL forms and toxicity scoring may also be completed via telephone for all follow up visits (but not preferred) if patient prefers or is unable to attend clinic. For non-English patients, a fluent family member, staff, or professional translator may assist with completion of the questionnaire. The FACT-E and FACT-L are also available in the following languages (contact the coordinating centre or [www.facit.org](http://www.facit.org) for these):

Chinese (simplified or traditional), Dutch, French, German, Hungarian, Italian, Japanese, Polish, Spanish

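### Nothing in the protocol keeps arm-aware treating staff from administering the self-report QoL forms: a physician may take them by telephone at weeks 4 and 8, and the interviewer or helper at the primary 2-week visit is unrestricted

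*Protocol*

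**What the plan says.** **Outcome.** Section 2.1 defines the primary endpoint as esophageal quality of life, "Measured by the Esophageal Cancer Subscale (ECS) of the FACT-E". Section 10.5 fixes the time point: "Esophageal quality of life will be calculated by tabulating FACT-E scores at 2 weeks". The form in Appendix 4 is a self-report questionnaire.

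**Section 9.0.** Patients are to be seen at 2 weeks, and the questionnaires are collected at every visit. If the treating physician or the patient prefers, "visits at 4 and 8 weeks may be substituted with a telephone interview". Two kinds of interviewer are named: "telephone interview (by the research coordinator or physician) to complete quality of life questionnaires and toxicity data".

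**Appendix 2.** The footnote to the follow-up schedule is wider: "QoL forms and toxicity scoring may also be completed via telephone for all follow up visits". It marks this route as not the preferred one, for a patient who wants it or cannot come to clinic, and does not say who makes the call. It adds: "For non-English patients, a fluent family member, staff, or professional translator may assist with completion of the questionnaire". It lists languages in which the FACT-E and FACT-L can be obtained, but does not require that version before help is given.

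**Knowledge of the arm.** Section 6.5: "If the patient is eligible the coordinating centre will confirm via email and provide the randomization arm". The radiation oncologist signs the Arm 1 fields before randomization (section 6.04), and Arm 2 needs an IMRT plan (section 6.2). The only masking described is that of the DSMC at the interim analysis (section 10.6).

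**The concern.** The ECS asks about swallowing, pain on swallowing and enjoyment of meals. Answers given aloud to someone who planned or delivered either standard or esophageal-sparing treatment are open to prompting and to the wish to please. If that influence differs by arm, it adds directly to the treatment difference. Neither baseline adjustment nor a mixed model removes it, and an analysis plan cannot repair forms already collected that way.

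Exposure differs by visit. At weeks 4 and 8 the physician interviewer is written into the protocol. These scores enter the linear mixed-effects QoL models and the utilities for the cost-effectiveness analysis (section 10.5). At week 2 the exposure is an omission: the telephone interviewer is not named, and staff who help non-English patients need not be outside the treating team.

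**Working it through.** **1. The passages by visit**

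| Point | Weeks 4 and 8 | Week 2 (primary) |
|---|---|---|
| Telephone allowed? | Yes: section 9.0 and Appendix 2 | Appendix 2 only; section 9.0 has the patient seen |
| Trigger | Section 9.0: preference of physician or patient | Patient prefers it or cannot attend; not the preferred route |
| Interviewer | Coordinator or physician | Not named |
| Staff help | Non-English patients | Non-English patients |
| Independence from treating team or masking required? | No | No |

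Section 9.0 and Appendix 2 therefore also disagree on which visits may be done by telephone.

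**2. The plan's own sample size**

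Inputs from section 10.4: effect size 0.65, two-sided alpha 0.05, power 80%, non-response 15%.

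- n per arm = 2(1.960 + 0.842)² / 0.65² = 37.2, rounded up to 38.
- 38 / 0.85 = 44.7, rounded up to 45 per arm, 90 in total.

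The stated 90 reproduces and is not in dispute. The evaluable number used below is 38 per arm.

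**3. What an arm-dependent influence would do to the primary test**

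The protocol gives neither the share *f* of 2-week forms taken or assisted by arm-aware treating staff nor the shift in such forms. Both are assumptions here: the shift is set at 0.5 SD and *f* is varied. With no true effect:

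- bias in the mean difference: b = 0.5 × *f* (in SD)
- noncentrality: b × √(38/2) = 4.359 × b, with 74 degrees of freedom
- rejection rate: probability that |t| exceeds 1.993

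The SD implied by section 10.4, if 2 to 3 points is the 0.65 SD effect, is 2/0.65 = 3.08 to 3/0.65 = 4.62 points.

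| *f* | b (SD) | Bias in ECS points | False-positive rate |
|---|---|---|---|
| 5% | 0.025 | 0.08 to 0.12 | 5.1% |
| 10% | 0.05 | 0.15 to 0.23 | 5.5% |
| 20% | 0.10 | 0.31 to 0.46 | 7.1% |
| 40% | 0.20 | 0.62 to 0.92 | 13.8% |

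With a smaller influence of 1 point per affected form and *f* = 10%, b = 0.022 to 0.033 SD and the rate is 5.1% to 5.2%.

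**The case against.** The main quoted sentence covers weeks 4 and 8, not the primary time point. A reader might infer that the protocol lets the treating physician take the primary form. The documents do not support that: no section names a physician interviewer at week 2, section 9.0 says physician rather than treating physician, and telephone at week 2 is a disfavoured fallback. What stands is narrower: nothing excludes such a person at week 2.

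The 0.5 SD shift is also large. It is 0.5/0.65 = 77% of the effect the trial is powered for, and its direction, though plausibly in favour of Arm 2, is assumed too. This is accepted. If few forms are affected, the distortion of the primary test is close to nil.

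The remedy is partial. The coordinator's site is told the arm, and the protocol describes no masking of patients, so expectation effects remain whoever reads the items. This also stands.

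Finally, flexible completion protects response in a palliative ECOG 0-3 population in which 15% non-response is already assumed. That is a reason to keep telephone completion and family help, as the fix does. It is not a reason to keep the treating team in the role, since the coordinator is already the named alternative.

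**Conclusion.** The point holds as a gap in outcome ascertainment. At weeks 4 and 8 a physician, who may be the arm-aware treating physician, is a permitted administrator of self-report forms that feed secondary QoL and utility analyses. At week 2 the protocol leaves the same possibility open without stating it.

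The effect on the primary test cannot be derived from the protocol. Under the assumed 0.5 SD shift it runs from negligible (5.1% at 5% of forms) to material (13.8% at 40%). The sample size is unaffected. The change is worth making because it is cheap and must precede data collection, not because a large bias has been shown. Confidence is medium: that the trial is unmasked is inferred from the absence of any masking of patients or site staff, and the number of telephone or assisted forms is unknown.

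**What to change.** - **Section 9.0:** delete the words *or physician* for the questionnaires. Toxicity recording may stay with the physician.
- **Appendix 2:** state that the treating physician and staff who plan or deliver the radiotherapy do not administer or help complete the FACT-E, FACT-L or EQ-5D at any visit; that telephone forms are read verbatim by the research coordinator; and that at the 2-week visit the patient completes the form before seeing the oncologist.
- **Language:** use a listed language version where there is one; otherwise family or a translator outside the treating team may help.
- **Consistency:** make section 9.0 and Appendix 2 agree on which visits may be done by telephone.
- **Data:** record mode and helper for each form in REDCap and report both by arm. An analysis restricted to self-completed forms is supportive only. It selects on a post-randomization variable: patients who cannot attend may be sicker, possibly from esophagitis itself.

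**Cost:** protocol wording and fields for mode and helper on the form; no change to N and no added role. The downside is slightly less flexibility in who may make calls. The coordinator and the patients may still know the arm, so the bias is reduced, not removed.
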